## Abstract

**Background:**

The social environment at schools is an important setting to promote educational attainment, and health and well-being of young people. However, within upper secondary education there is a need for evidence-based school intervention programmes. The Shaping the Social intervention is a comprehensive programme integrating social and educational activities to promote student well-being and reduce smoking and dropout in upper secondary vocational education. The evaluation design is reported here.

**Methods/design:**

The evaluation employed a non-randomised cluster controlled design, and schools were selected to either implement the intervention or continue with normal practice for comparison. In the baseline survey conducted 2011–2012, 2,329 students from four intervention schools and 3,371 students from six comparison schools answered a computer-based questionnaire during class, representing 73 % and 81 % of eligible students, and 22 % of all technical/agricultural vocational schools in Denmark. Follow-up assessment was conducted 10 weeks after baseline and at the same time teachers of the intervention classes answered a questionnaire about implementation. School dropout rates will be tracked via national education registers through a 2-year follow-up period.

**Discussion:**

Shaping the Social was designed to address that students at Danish vocational schools constitute a high risk population concerning health behaviour as well as school dropout by modifying the school environment, alongside developing appropriate evaluation strategies. To address difficulties in implementing settings-based interventions, as highlighted in prior research, the strategy was to involve intervention schools in the development of the intervention. Baseline differences will be included in the effectiveness analysis, so will the impact of likely mediators and moderators of the intervention.

**Trials registration:**

ISRCTN57822968. Date of registration: 16/01/2013

## Background

Schools are important settings for health promotion in young people [1–5]. Health education aiming to improve knowledge, develop skills and modifying norms is frequently used in schools, for example addressing substance use. However, such interventions often have disappointing results [6, 7]. In recent years there has been an increased recognition of how modifying the school social and/or physical environment can promote students’ health [8–10]. For example, a review found that class restructuring programs in which students spend more time with teachers were effective in decreasing school dropout [10]. Such a comprehensive approach is also known as the healthy school setting approach [11]. However, the evidence for this approach is relatively weak, in part because of difficulties related to both implementation and evaluation [12].

Several longitudinal studies have shown that harmful substance use predicts poor educational achievement [13, 14] and that educational failure is predictive of harmful substance use [15, 16]. Thus, a comprehensive perspective on both health risk behaviour and school dropout should be considered in intervention programmes aiming at promoting health and educational attainment.

In Denmark, approximately half of students drop out of vocational schools, which is a much higher rate compared to 18 % high school dropout [17]. The educational programme at vocational schools consist of a short basic course (typically 10–40 weeks) followed by a main course. Most dropout occurs during basic training. In addition, students more often engage in health risk behaviour compared to high school students [18]. For example, 23 % of vocational students and 9 % of high school students have tried drugs other than cannabis [18].

Ethnographic fieldwork performed at basic courses in Danish vocational schools indicates that vocational schools do not prioritise the development of social relations [19]. Students primarily work individually, and there is little time for social activities [19]. Students’ lack of social relationships in school can disrupt their educational pursuits. Young people who feel that they do not fit in at school are less likely to show up at school [1]. Previous research found that students who dropped out had low academic motivation, felt socially excluded, and did not have stable supportive adults [20]. In Danish vocational schools, smoking plays a central role in social interactions, and thus the students’ focus drifts away from achievement of professional skills [19]. This suggests that the school context enhances the use of cigarettes [21, 22]. Moreover, the relationship between academic achievement and substance use might be dynamic [23], so students with lower levels of academic achievement are more likely to engage in cigarette smoking.

In spite of the ample research evidence that points at the significance of the social environment for educational attainment, and the health and well-being of young people, little is known of specific intervention programmes that may be put to use in the context of vocational training. The aim of Shaping the Social was to develop and evaluate an intervention that promotes academic and social integration in vocational students to improve well-being, and reduce smoking and dropout in Danish vocational schools. Academic integration refers to students’ development of a strong affiliation with the school academic environment, including perceived fit with the educational programme and academic interactions with school staff, whereas social integration refers to development of a strong affiliation with the school social environment, including peer group interactions and informal contact with school staff [24].

We use a healthy setting approach. The healthy setting approach is criticized that it has a relatively weak evidence base for efficacy [12, 25]. This criticism should be seen in light of the fact that few studies focus on comprehensive programs and there are problems with both implementation and evaluation [12, 26]. Considering these limitations, there is a need for research on interventions with many components which in its design carefully take into account how initiatives are implemented and modified locally and what is an appropriate evaluation design. Therefore, this article aims to describe the evaluation strategies and response rates of Shaping the Social, a settings-based intervention study aimed to modify how the school environment influences well-being, smoking and dropout among students in upper secondary vocational education. In addition, we compare characteristics of the study population with the population from which it has been drawn in order to determine representativeness of the study sample.

## Methods

### Study design

Shaping the Social employed a non-randomised cluster controlled design with four intervention schools and six comparison schools. Comparison schools continued with their usual practice.

Intervention schools were selected by convenience sampling; the four schools involved in the development phase of the intervention agreed to become intervention schools. We chose this strategy in order to facilitate the implementation. The four intervention schools are located in major towns dispersed in Denmark and the schools are characterized as being large schools and offering a large range of technical or agricultural basic courses, for example carpenter and zookeeper. Characteristics of the intervention schools were used to select comparison schools among schools with the best match. However, a straight matched-pair design was not possible. Vocational schools in Denmark were ranked according to the following criteria: (1) at least one basic course offered for inclusion in the intervention group, (2) large school size (student population ≥ 800), (3) urban/suburban. Sixteen vocational schools were eligible. Subsequently, eight comparison schools were selected by geographic diversity. Letters explaining the study were sent to the school management, and schools expressing an interest (*n* = 7) were then visited individually. One school withdrew due to the time commitment entailed in the data collection. After selection of comparison schools, one intervention school wanted to include agricultural basic courses, which we accepted; however, the comparison schools were not selected on this criterion.

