### Participants

The study population consisted of students who attended the following basic courses (vocational clusters in brackets):Car mechanicsCarpenter, bricklayer, painter or plumber (Construction)Electrician, data technician or frontline PC supporter (Electricity and information and computing technology (IT))Media graphic designer, graphic technician, web integrator or sign writer (Media production)Zookeeper, landscaper, farmer or greenhouse gardener (Agricultural)

Shaping the Social is designed to accommodate the fact that this was a heterogeneous population considerably more diverse than, for example, a typical Danish high school population.

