### Evaluation methods

Initially, we will conduct scale validation of the student well-being outcome measure, which we hypothesise to be a four-factor model. Intervention effects will be evaluated by multilevel regression methods, specifically, a multilevel regression analysis accounting for the hierarchical data structure with students nested within classes in which the intervention was implemented, and classes nested within college units. We will use mediation analyses to explore the extent to which any intervention effects are mediated by changes in the measured immediate intervention impacts. The analyses will be conducted for the total study population. The smoking analysis will be repeated whereby students are analyzed according to their baseline smoking status. Analysis of subgroups will be conducted defined by age, parental socioeconomic status and basic course. To assess the stability of the available case analyses, handling of missing data will be conducted and analysis of loss to follow-up will indicate which variables to include.

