A second limitation is the lack of random allocation of the intervention between schools, which may introduce selection bias. However, analysis of the study sample and the research setting population showed that the study sample was representative of the population. Randomisation is not always possible when conducting school-based interventions [50]. First, there are a limited number of Danish vocational schools. Second, the schools involved in the development phase became intervention schools. This was necessary because the development phase facilitated the implementation, with time spent on internal organisation and integrating the intervention into the pre-existing school practices [51, 52]. We selected comparison schools in order to balance groups on important variables, such as type of basic course. Nevertheless, one basic course was included in the intervention group after selection of comparison schools. Whether unbalanced student characteristic impact outcomes will be examined and potentially controlled for in the analyses.

A third limitation is the time frame for baseline data collection. One substantially important design choice for the study was to collect baseline data during class in the first days of school – i.e., after the onset of the intervention – and this may contribute to underestimation of effects. When interpreting the results of the effect evaluation, the time frame for baseline data will be taken into account in the analyses.

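### Agricultural courses joined the intervention arm after the comparison schools were chosen without regard to them, yet the main analysis uses the total population with no firm commitment to adjust for course

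*Protocol article*

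**What the plan says.** All references are to the Protocol article.

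- **Study design.** Schools were ranked as possible comparators on three criteria. The one about courses was "at least one basic course offered for inclusion in the intervention group". The section then reports: "After selection of comparison schools, one intervention school wanted to include agricultural basic courses, which we accepted". It adds that "the comparison schools were not selected on this criterion".
- **Participants.** The agricultural cluster is one of five course groups making up the study population, with no restriction by arm.
- **Evaluation methods.** "The analyses will be conducted for the total study population". Also: "Analysis of subgroups will be conducted defined by age, parental socioeconomic status and basic course". The model is multilevel, with students in classes and classes in college units. Basic course is not named as a covariate.
- **Study strengths and limitations.** "We selected comparison schools in order to balance groups on important variables, such as type of basic course". The next sentence concedes that "one basic course was included in the intervention group after selection of comparison schools". The only handling offered there is that uneven student characteristics will be examined and may be adjusted for.
- **Abstract, Discussion.** Differences at baseline are to enter the effectiveness analysis. Course is not mentioned.

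**The concern.** The investigators wanted the arms to be alike in type of course, and the late addition works against that on one side only. If agricultural students differ from technical students in smoking, well-being or dropout for reasons unrelated to the programme, part of that difference becomes part of the arm contrast when everyone is analysed together. The Setting section makes such differences plausible: it describes departments as typically having their own premises and culture.

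The planned safeguards are weak for this purpose. Adjustment is conditional and worded for student characteristics. A random effect for college unit accounts for clustering but does not remove a systematic difference between course types. Table 1 marks well-being only at 10 weeks and dropout only at 2 years, so two of the three primary outcomes have no baseline value that could absorb a pre-existing course difference. The limitations section answers selection bias by pointing to the representativeness of the sample, but Table 2 pools both arms and says nothing about balance between them.

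**Working it through.** The plan gives no figure for the agricultural share or for outcome differences between courses. The check therefore has a planning effect taken from the article and a bias range resting on assumptions.

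**1. Planned effects (Sample size section: 20% relative reduction).**
- Daily smoking: 41% × 0.80 = 32.8%, a difference of 8.2 points.
- Considering dropping out: 19% × 0.80 = 15.2%, a difference of 3.8 points. This is the planning proxy, not register dropout.

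**2. Bias formula.** Let the agricultural share be s₁ in the intervention arm and s₀ in the comparison arm. Let D be the outcome difference between agricultural and other students in the absence of any intervention. Each arm's prevalence then moves by its share times D, so an unadjusted risk difference moves by

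bias = (s₁ − s₀) × D.

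**3. Assumed ranges.** s₁ − s₀ from 5 to 30 percentage points; D from 5 to 20 points. Neither range comes from the article.

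| s₁ − s₀ | D (points) | Shift (points) | Share of 8.2 (smoking) | Share of 3.8 (considering dropout) |
|---|---|---|---|---|
| 0.05 | 5 | 0.25 | 3% | 7% |
| 0.10 | 10 | 1.0 | 12% | 26% |
| 0.20 | 15 | 3.0 | 37% | 79% |
| 0.30 | 20 | 6.0 | 73% | 158% |

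The sign of D is unknown, so the shift could favour or disfavour the intervention.

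**4. What adjustment can do.**
- If both arms contain agricultural classes, a fixed effect for cluster compares like with like, and the bias above is removed to the extent that the model holds.
- If only the intervention arm contains them, the agricultural term in a model without a cluster-by-arm interaction is fitted from intervention students alone. The arm effect then comes in substance from the other clusters. Applying it to agricultural students is extrapolation, and an agricultural subgroup effect cannot be estimated.
- Without a course term, nothing in the stated model separates course from arm.

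**The case against.** A reader might infer that the comparison arm has no agricultural students, so that this course is wholly confounded with arm and its subgroup contrast is impossible. The article does not support that. It says the comparison schools were chosen without regard to agriculture, not that they lack it. The Participants section lists the cluster for the whole study population, and Participant flow describes the ten schools together as technical and agricultural. Neither statement shows that comparison schools supplied such students, but absence is not shown either.

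Two related inferences also go too far. Comparison schools were not matched on the full list of courses: one shared course was enough, and the article says a straight matched-pair design was not possible. For the same reason it cannot be taken as given that the other four clusters appear in both arms.

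In the plan's favour, the late addition is openly disclosed, and adjustment for baseline differences is announced. Subgroup analyses by course would show the technical clusters separately. Smoking is measured at baseline, and its analysis is to be repeated by baseline smoking status, which gives that outcome some protection. A complete covariate list may properly sit in a fuller document that is not shown. Finally, the bias range is assumed and its lower end is trivial.

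These points limit the claim but do not dispose of it. The article itself names course as important for balance, reports that the balance was disturbed on one side, and then describes the main analysis without tying it to course. A subgroup display does not correct the pooled estimate, and well-being and dropout lack the baseline value that helps with smoking.

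**Conclusion.** The concern holds as a risk of confounding, not as a demonstrated bias. Agricultural students may be over-represented in, or confined to, the intervention arm, and the total-population analysis is stated with only conditional adjustment. Under the assumed ranges, an unadjusted contrast would shift by 0.25 to 6 points, or 3% to 73% of the planned 8.2-point smoking effect. The true shift could be negligible, and its direction is unknown. The conclusion rests on two quantities the article does not give: the agricultural share in each arm, and the outcome difference between agricultural and other students. A count of classes by cluster and arm would settle whether there is a comparator at all.

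**What to change.** 1. Include vocational cluster as a fixed effect in all primary effect models, instead of leaving it to an examination of imbalance.
2. Tabulate students and classes by cluster and arm for all five clusters.
3. Name an analysis restricted to the clusters with classes in both arms, at least as a sensitivity analysis. Let the table decide which clusters qualify. Making this population primary is open to debate, because the Study status section says data are already being analysed.
4. If the comparison arm has no agricultural classes, report agricultural students descriptively and base the effect conclusion on the overlapping clusters.

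Cluster is defined by the course each student entered, so no new data are needed. The cost is wording, one table and one extra analysis, with slightly lower precision and some intervention students left out of the restricted estimate. The choice should be recorded before effect estimates are seen or, if they have been seen, labelled as made afterwards.

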### Intervention content

Shaping the Social is a collection of intervention components to be used by school management and teachers in the intervention group; listed below. A detailed description of the intervention and the developmental work, including theories adapted and ethnographic fieldwork conducted for rationalising the intervention, is described elsewhere [19].A preliminary meeting at the school with a teacher, the students and their relativesWelcoming activities: Preparing classrooms, a welcome speech, an updated list of students, a round of person-to-person introductions, products of older students should be displayed and the students should begin working on an assignment relevant to their education, preferably in groups.Timetable with a clear description of course, time, place and clothing requirementsDaily class meetings with mandatory participation for all students and their teachers. Coffee/the is served and the curriculum for the day is planned.Scheduled breaks: All students take breaks at the same time, and smoking is only allowed during the scheduled breaksPleasant non-smoking place to hang out during breaks is set upMonthly events during school hours across sections (optional component)Open workshop with student access to school facilities outside school hours and a teacher present (optional component)

A staff pamphlet was developed with a description of the intervention components, and the intended immediate impacts of these components. During the study period, intervention schools had regularly contact with the research team, some departments more intensively because a formative process evaluation was conducted; description of the process evaluation itself is beyond the scope of this article.

Figure 1 outlines the programme theory of Shaping the Social. Reduced school dropout is hypothesised to be caused by intervention efforts to improve student well-being and reduce the frequency of cigarette smoking during school hours. Intervention-induced improvements in student well-being and smoking are hypothesised to be caused by improved academic and social integration. Measuring these mediating processes should facilitate the understanding of short-term programme effects on student well-being and smoking. In addition, we measured whether the intervention was implemented as intended. Figure 1 also reflects our recognition that the magnitude of the intervention’s impact may depend on several moderating student characteristics.

**Fig. 1 Fig1:**
[figure not shown]
The hypothesised causal relationship between Shaping the Social intervention programme and proximal and distal outcomes

### Setting

After nine compulsory years of primary and lower secondary school, almost all young people of Denmark choose to continue into the academically oriented upper secondary schools system, which is preparing students for tertiary education or into vocational education organized in separate schools spread out across large and medium sized cities. About 23% will choose vocational education [27]. Vocational education includes commercial, agricultural, technical, and social and healthcare programs leading to professions such as farmer, carpenter or web integrator. All programs are initiated by a school-based basic course lasting 20–25 weeks. The basic courses usually started four times a year and are flexible in duration depending on the student’s prior qualifications and ambitions. This means that some students within a class finish the basic course before others, and therefore a class is not a definite unit. Additionally, the high dropout rate implies that classes are merged during the basic course. We defined a class as students entering the same programme (e.g., carpenter) on the same date at the same address.

The vocational schools are organized into two levels. The upper level is the school with a management board. Next level is departments (e.g., construction) which are each headed by an inspector, one or more educational managers and an administration manager, and, typically, the departments have separate physical area and culture. In Shaping the Social, the upper analyze level will be these departments within schools (named college units).

